##### **Grade IIIa**

Intervention not under general anesthesia

##### **Grade IIIb**

Intervention under general anesthesia

##### **Grade IV**

Life-threatening complication (including CNS complications) requiring IC/ICU-management

##### **Grade IVa**

[figure not shown]

Single organ dysfunction (including dialysis)

**Grade IVb**

Multiple organ dysfunction

**Grade V**

Death of a patient

## 9.2 Adverse events (AEs)

### 9.2.1 Summary of known and potential risks of the study drug

The overall safety experience with nivolumab, as monotherapy or in combination with ipilimumab, is based on experience in approximately 12,300 subjects treated to date. Extensive details on the safety profile of nivolumab and ipilimumab, including results from other clinical studies, are available in section 5.6 of the nivolumab IB or ipilimumab IB and will not be repeated herein.

Overall, the safety profile of nivolumab in combination with ipilimumab or radiotherapy is manageable and generally consistent across completed and ongoing clinical trials. Most AEs were low-grade (Grade 1 to 2) with relatively few related high-grade (Grade 3 to 4) AEs. There was no pattern in the incidence, severity, or causality of AEs with respect to nivolumab dose level. Results to date suggest that the safety profile of nivolumab/ipilimumab combination therapy and nivolumab in combination with radiotherapy is consistent with the mechanisms of action of nivolumab and ipilimumab. The nature of the AEs is similar to that observed with either agent used as monotherapy; however, both frequency and severity of most AEs are increased with the combination.

A pattern of immune-related AEs has been defined, for which management algorithms have been developed; these are provided in nivolumab IB/SmPC or ipilimumab IB/SmPC. Most high-grade events were manageable with the use of corticosteroids or hormone replacement therapy (endocrinopathies) as instructed in these algorithms. For additional material, see the nivolumab IB/SmPC and ipilimumab IB/SmPC.

### 9.2.2 Definition of adverse events

An adverse event (AE) is defined as any new untoward medical occurrence or worsening of a preexisting medical condition in a clinical investigation participant administered study drug and that does not necessarily have a causal relationship with this treatment. An AE can therefore be any unfavorable and unintended sign (such as an abnormal laboratory finding), symptom, or disease temporally associated with the use of investigational product, whether or not considered related to the investigational product.

A **non-serious adverse event** is an AE not classified as serious.

## 9.3 Serious adverse events (SAEs)

A serious adverse event (SAE) is any untoward medical occurrence that at any dose:

- results in death

[figure not shown]

- is life-threatening (defined as an event in which the participant was at risk of death at the time of the event; it does not refer to an event which hypothetically might have caused death if it were more severe)
- requires inpatient hospitalization or causes prolongation of existing hospitalization (see **NOTE** below)
- results in persistent or significant disability/incapacity
- is a congenital anomaly/birth defect
- is an important medical event (defined as a medical event(s) that may not be immediately life-threatening or result in death or hospitalization but, based upon appropriate medical and scientific judgment, may jeopardize the subject or may require intervention [eg, medical, surgical] to prevent one of the other serious outcomes listed in the definition above.) Examples of such events include, but are not limited to, intensive treatment in an emergency room or at home for allergic bronchospasm; blood dyscrasias or convulsions that do not result in hospitalization.)
- Suspected transmission of an infectious agent (*i.e.* pathogenic or nonpathogenic) via the study drug is an SAE.

Although pregnancy and potential drug-induced liver injury (DILI), are not always serious by regulatory definition, however, these events must be reported within the SAEs timeline.

Any component of a study endpoint that is considered related to study therapy should be reported as an SAE (*i.e.* death is an endpoint, if death occurred due to anaphylaxis, anaphylaxis must be reported).

### 9.3.1 Hospitalization – Prolongation of existing hospitalization

Hospitalization is defined as an overnight stay in a hospital unit and/or emergency room. An additional overnight stay defines a prolongation of existing hospitalization.

**The following is not considered an SAE and should be reported as an AE only:**

- Treatment on an emergency or outsubject basis for an event not fulfilling the definition of seriousness given above and not resulting in hospitalization.

**The following reasons for hospitalizations are not considered AEs, and therefore not SAEs:**

- Hospitalizations for cosmetic elective surgery, social and/or convenience reasons.
- Elective treatment of a pre-existing disease or medical condition that did not worsen, *i.e.* hospitalization for chemotherapy for cancer, elective hip replacement for arthritis.
- A visit to the emergency room or other hospital department < 24 h, that does not result in admission (unless considered an important medical or life-threatening event)
- Elective surgery, planned prior to signing consent
- Admissions as per protocol for a planned medical/surgical procedure
- Routine health assessment requiring admission for baseline/trending of health status (*i.e.* routine colonoscopy)

[figure not shown]

- Medical/surgical admission other than to remedy ill health and planned prior to entry into the study. Appropriate documentation is required in these cases.
- Admission encountered for another life circumstance that carries no bearing on health status and requires no medical/surgical intervention (*i.e.* lack of housing, economic inadequacy, caregiver respite, family circumstances, administrative reason).
- Admission for administration of anticancer therapy in the absence of any other SAEs (applies to oncology protocols)

### 9.3.2 SAEs related to investigational drug

Such SAEs are defined as SAEs that appear to have a reasonable possibility of causal relationship.

### 9.3.3 Suspected unexpected serious adverse reactions (SUSARs)

SUSARs are all serious adverse reactions with **suspected** causal relationship to the study drug that is **unexpected** (not previously described in the SmPC or IB) and serious.

### 9.3.4 Pregnancy

If, following initiation of the investigational product, it is subsequently discovered that a study participant is pregnant or may have been pregnant at the time of investigational product exposure, including during at least 5 half-lives after product administration, the investigational product will be permanently discontinued in an appropriate manner (*i.e.* dose tapering if necessary for participant).

The investigator must immediately notify [contact] of this event and complete one of the following forms within 24 h of awareness of the event via either the CIOMS, MedWatch or appropriate Pregnancy Surveillance Form in accordance with SAE reporting procedures.

Protocol-required procedures for study discontinuation and follow-up must be performed on the participant.

Follow-up information regarding the course of the pregnancy, including perinatal and neonatal outcome and, where applicable, offspring information must be reported on the CIOMS, MedWatch, BMS Pregnancy Surveillance Form, or approved site SAE form. A BMS Pregnancy Surveillance Form may be provided upon request.

Any pregnancy that occurs in a female partner of a male study participant should be reported to BMS. Information on this pregnancy will be collected on the Pregnancy Surveillance Form. In order for Sponsor or designee to collect any pregnancy surveillance information from the female partner, the female partner must sign an informed consent form for disclosure of this information.

## 9.4 Severity of adverse events

The severity of clinical AEs is graded on the latest Common Terminology Criteria for Adverse Events (CTCAE) [27] and reported on specific AE pages of the eCRF.

[figure not shown]

#### **Grade 1**

Mild; Asymptomatic or mild symptoms; clinical or diagnostic observations only; intervention not indicated.

#### **Grade 2**

Moderate; Minimal, local or noninvasive intervention indicated; limiting age-appropriate instrumental Activities of Daily Living (ADL; refer to preparing meals, shopping for groceries or clothes, using the telephone, managing money, etc).

#### **Grade 3**

Severe or medically significant but not immediately life-threatening; Hospitalization or prolongation of hospitalization indicated; disabling; limiting self-care ADL (refer to bathing, dressing and undressing, feeding self, using the toilet, taking medications, and not bedridden).

#### **Grade 4**

Life-threatening consequences; Urgent intervention indicated.

#### **Grade 5**

Death related to AE.

## **9.5 Relationship to study drug**

For all AEs, the Investigator will assess the causal relationship between the study drug and the AE using his/her clinical expertise and judgment according to the following algorithm that best fits the circumstances of the AE:

#### **Not related**

- May or may not follow a temporal sequence from administration of the study product
- Is biologically implausible and does not follow known response pattern to the suspect study drug (if response pattern is previously known).
- Can be explained by the known characteristics of the subject's clinical state or other modes of therapy administered to the subject.

#### **Related**

- Reasonable temporal relation between the AE and the intake of the study medication and
- There is no other explanation for the AE and
- Subsidence or disappearance of the AE on withdrawal of the study medication and
- Recurrence of the symptoms on restart at previous dose (only applies for re-institution of medication).

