**SAE Email Address:** [[contact]](mailto:[contact])

**SAE [contact]

If only limited information is initially available, follow-up reports are required. (Note: Follow-up SAE reports should include the same investigator term(s) initially reported.)

If an ongoing SAE changes in its intensity or relationship to study drug or if new information becomes available, a follow-up SAE report should be sent within 24 h \ 1 Business Day to BMS using the same procedure used for transmitting the initial SAE report.

All SAEs should be followed to resolution or stabilization.

The causal relationship to study drug is determined by a physician and should be used to assess all adverse events (AE). The causal relationship can be one of the following:

Related: There is a reasonable causal relationship between study drug administration and the AE.

Not related: There is not a reasonable causal relationship between study drug administration and the AE.

The term "reasonable causal relationship" means there is evidence to suggest a causal relationship.

Adverse events can be spontaneously reported or elicited during open-ended questioning, examination, or evaluation of a subject. (In order to prevent reporting bias, subjects should not be questioned regarding the specific occurrence of one or more AEs.)

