#### 11.4.4 Safety and tolerability endpoints

The safety analysis will be performed in all participants who have received at least 1 dose of study treatment. Descriptive statistics of safety will be presented using latest NCI CTCAE by treatment arm. Adverse events, treatment-related AEs, SAEs and treatment-related SAEs will be tabulated using worst grade per latest NCI CTCAE criteria by system organ class and preferred term. On-study lab parameters including hematology, chemistry including liver function and renal function will be summarized using worst grade per latest NCI CTCAE criteria.

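### Sections 9.3.2, 9.5 and 9.6 set incompatible causality tests for one related / not related field; read literally, 9.5 under-attributes toxicity to ipilimumab and nivolumab

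*Protocol*

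**What the plan says.** Section 9.5 tells the investigator to judge causality for every AE and gives two lists. Under Related, the criteria are joined by a conjunction: "Reasonable temporal relation between the AE and the intake of the study medication and", then "There is no other explanation for the AE and", then "Subsidence or disappearance of the AE on withdrawal of the study medication and". A fourth item, recurrence on restart, applies only if the drug is given again. Under Not related, one item reads "Can be explained by the known characteristics of the subject's clinical state or other modes of therapy administered to the subject".

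Section 9.6 defines the same word differently: "There is a reasonable causal relationship between study drug administration and the AE". It explains that this means evidence suggesting a causal link, and says the assessment is to be used for all AEs. Section 9.3.2 has a third wording, for serious events: "SAEs that appear to have a reasonable possibility of causal relationship".

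The eCRF item listed in section 9.6 under Other Safety Considerations is a single related / not related entry. It is completed according to criteria stated earlier in the text, without saying which. Section 11.4.4 then uses the result: "Adverse events, treatment-related AEs, SAEs and treatment-related SAEs will be tabulated".

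**The concern.** One event can be related under one section and not related under another, so the recorded value depends on which page the investigator follows. The two tests also differ in a known direction. The 9.5 test asks that other causes be excluded and that the event subside on withdrawal. Both demands fit poorly with a regimen in which the investigational drugs are added to radiotherapy and capecitabine, followed by surgery, and in which one of the drugs is given once.

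At stake are the treatment-related AE and SAE tables in a trial whose primary objective is safety and tolerability, assessed partly by CTCAE (section 6.1). Consistency of SUSAR identification is also at stake, because it depends on a judgement about the drug's causal role. An analysis plan could not repair attributions that were recorded under mixed rules.

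**Working it through.** There is no plan figure to reproduce. The check sets the definitions side by side and places the dosing against the other treatments.

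**1. The definitions compared**

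| Requirement | 9.5 Related | 9.6 Related | 9.3.2 (SAEs) |
|---|---|---|---|
| Stated scope | all AEs | all AEs | SAEs |
| Temporal relation | required | not named | not named |
| Other explanations excluded | required | no | no |
| Subsidence on withdrawal | required | no | no |
| Recurrence on restart | required if restarted | no | no |
| Threshold | all of the above | evidence suggesting a causal link | reasonable possibility |

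So 9.5 has three criteria that always apply and a fourth that applies conditionally.

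**2. Direction of the difference.** An event that meets every 9.5 criterion also has evidence suggesting a causal link, so it meets 9.6. The converse fails. Hence the related count under 9.5 is at most the related count under 9.6, and the error can run only toward under-attribution.

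**3. Overlap with other treatment** (section 8.2.3, section 7.1.5, Table 4), assuming CRT starts on time and is not interrupted:
- CRT: 25 working days, Monday to Friday, is 25 / 5 = 5 weeks, to about day 35.
- Infusions: ipilimumab on day 7; nivolumab on days 14, 28 and 42.
- Days 7, 14 and 28 fall within CRT, so 3 of 4 infusions (2 of 3 for nivolumab). Day 42 comes 42 − 35 = 7 days after it.
- Surgery: weeks 15 to 17, that is days 15 × 7 = 105 to 17 × 7 = 119.
- AE collection runs at least 100 days after the last dose: 42 + 100 = day 142. Surgery therefore falls inside it and adds another possible explanation.

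**4. Event types under each test**

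| Event | 9.5 read literally | 9.6 / 9.3.2 |
|---|---|---|
| Toxicity that CRT could also cause | fails the no-other-explanation criterion | can be related |
| Event after the single ipilimumab dose that persists | no later ipilimumab dose to withhold; fails subsidence | can be related |
| Event starting after the last nivolumab dose (day 42) that persists | same | can be related |
| Persistent endocrinopathy needing hormone replacement (mentioned in 9.2.1) | fails subsidence, even if CRT is no explanation | can be related |
| Fatal event | cannot subside | can be related |

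Section 9.2.1 also says that most high-grade events were manageable with corticosteroids or hormone replacement. Improvement under such treatment need not show a withdrawal effect.

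**The case against.** The best defence is that section 9.5 is not mechanical. It refers to clinical expertise and to the algorithm that best fits the event. Whether another explanation exists is a judgement on the individual case, the Not related list has no stated connectors, and section 9.6 may already be the operative rule because it too covers all AEs. This stands as a limit on how often misclassification would occur. It does not remove the contradiction: the judgement is to be exercised according to the 9.5 lists, and nothing ranks 9.5 against 9.6.

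A reader might infer three stronger things that the documents do not support.

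- *That almost no event could ever be related under 9.5.* An immune-related event that CRT does not explain and that subsides can pass, and the recurrence criterion is conditional.
- *That reportable events would be missed.* Section 9.6 sends all SAEs within the window to the manufacturer whatever their causality, with reconciliation every three months, and collects all non-serious AEs. Section 9.3.3 defines SUSARs by a suspected relationship and does not cite 9.5. The risk is inconsistent labelling. Only SAEs after the window depend for reporting on a belief that they are related to the study drug or a protocol procedure.
- *That the main safety conclusion is biased.* The rules in the synopsis, section 11.4.2 and section 11.4.6 count complications and reoperations without attribution.

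**Conclusion.** The contradiction is real and should be corrected. Three sections state different causality thresholds for one binary field, and the strictest does not suit concurrent CRT or a single-dose drug. Where investigators follow 9.5 literally, the treatment-related AE and SAE counts are biased downward, in favour of the combination, and SUSAR classification may vary between investigators.

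The size cannot be calculated. The protocol gives neither the rate of overlapping toxicities nor any indication of which definition sites would use. That all 50 planned treatment-arm patients are due to receive CRT describes exposure and is not a count of misclassified events. The conclusion rests on reading the 9.5 conjunctions as written and on CRT running to schedule. All-cause AE and SAE tables, which section 11.4.4 already plans by arm, do not depend on the label.

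**What to change.** Delete the two criteria lists in section 9.5. Use one definition, a reasonable possibility of a causal relationship, in sections 9.3.2, 9.5 and 9.6, for all AEs and SAEs. State that the eCRF field is completed under that definition and that the tables in section 11.4.4 use it.

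The cost is a short protocol amendment and matching eCRF guidance. The related-event count may be higher, and so less favourable, and that should be accepted. Recording attribution separately for ipilimumab, nivolumab and CRT (three fields in place of one) would make overlap visible, but it is optional and not needed to remove the contradiction. No new all-cause table is required.

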## **9.6 Reporting procedures**

- All Serious Adverse Events (SAEs) that occur following the subject's written consent to participate in the study through 100 days of discontinuation of dosing must be reported to BMS Worldwide

[figure not shown]

Safety, whether related or not related to study drug. If applicable, SAEs must be collected that relate to any later protocol-specified procedure (*i.e.* a follow-up biopsy).

- Following the subject's written consent to participate in the study, all SAEs, whether related or not related to study drug, are collected, including those thought to be associated with protocol-specified procedures. The investigator should report any SAE occurring after these aforementioned time periods, which is believed to be related to study drug or protocol-specified procedure.
- An SAE report should be completed for any event where doubt exists regarding its seriousness;
- If the investigator believes that an SAE is not related to study drug, but is potentially related to the conditions of the study (such as withdrawal of previous therapy or a complication of a study procedure), the relationship should be specified in the narrative section of the SAE Report Form.

An appropriate SAE form (*i.e.* ex-US = CIOMS form or USA = Medwatch form) should be used to report SAEs to BMS. If you prefer to use your own Institutional form, it must be reviewed by the BMS Protocol Manager prior to study initiation to ensure that at a minimum all of the data elements on the CIOMS form are present. The BMS Protocol number will be included on the SAE form or on the cover sheet with the SAE form transmission.

- The CIOMS form is available at: <http://www.cioms.ch/index.php/cioms-form-i>
- The MedWatch form is available at: [MedWatch 3500 Form](#)
- For studies with long-term follow-up periods in which safety data are being reported, include the timing of SAE collection.
- The Sponsor will reconcile the clinical database AE cases (**case level only**) transmitted to BMS Global Pharmacovigilance ([[contact]](mailto:[contact])).
  - The Investigator will request from BMS GPV&E, [[contact]](mailto:[contact]) the SAE reconciliation report and include the BMS protocol number every 3 months and prior to data base lock or final data summary
  - GPV&E will send the investigator the report to verify and confirm all SAEs have been transmitted to BMS GPV&E.
  - The data elements listed on the GPV&E reconciliation report will be used for case identification purposes. If the Investigator determines a case was not transmitted to BMS GPV&E, the case should be sent immediately to BMS ([[contact]](mailto:[contact])).
- In addition to the Sponsor Investigator's responsibility to report events to their local HA, suspected serious adverse reactions (whether expected or unexpected) shall be reported by BMS to the relevant competent health authorities in all concerned countries according to local regulations (either as expedited and/or in aggregate reports).
- In accordance with local regulations, BMS will notify sponsor investigators of all reported SAEs that are suspected (related to the investigational product) and unexpected (*i.e.* not previously described in the IB). An event meeting these criteria is termed a Suspected, Unexpected Serious Adverse Reaction (SUSAR). Sponsor investigator notification of these events will be in the form of either a SUSAR Report or a Semi-Annual SUSAR Report.
  - Other important findings which may be reported by BMS as an Expedited Safety Report (ESR) include: increased frequency of a clinically significant expected SAE, an SAE considered associated with study procedures that could modify the conduct of the study, lack of efficacy that poses significant hazard to study subjects, clinically significant safety finding from a nonclinical (*i.e.* animal) study, important safety recommendations

[figure not shown]

from a study data monitoring committee, or sponsor or BMS decision to end or temporarily halt a clinical study for safety reasons.

- Upon receiving an ESR from BMS, the investigator must review and retain the ESR with the IB. Where required by local regulations or when there is a central IRB/IEC for the study, the sponsor will submit the ESR to the appropriate IRB/IEC. The investigator and IRB/IEC will determine if the informed consent requires revision. The investigator should also comply with the IRB/IEC procedures for reporting any other safety information.

SAEs, whether related or not related to study drug, and pregnancies must be reported to BMS within 24 h \ 1 Business Day of becoming aware of the event. SAEs must be recorded on either CIOMS, MedWatch, or approved site SAE form.

Pregnancies must be reported and submitted to BMS. BMS will perform due diligence follow-up using the BMS Pregnancy Form which the investigator must complete.

**SAE Email Address:** [[contact]](mailto:[contact])

**SAE [contact]

If only limited information is initially available, follow-up reports are required. (Note: Follow-up SAE reports should include the same investigator term(s) initially reported.)

If an ongoing SAE changes in its intensity or relationship to study drug or if new information becomes available, a follow-up SAE report should be sent within 24 h \ 1 Business Day to BMS using the same procedure used for transmitting the initial SAE report.

All SAEs should be followed to resolution or stabilization.

The causal relationship to study drug is determined by a physician and should be used to assess all adverse events (AE). The causal relationship can be one of the following:

Related: There is a reasonable causal relationship between study drug administration and the AE.

Not related: There is not a reasonable causal relationship between study drug administration and the AE.

The term "reasonable causal relationship" means there is evidence to suggest a causal relationship.

Adverse events can be spontaneously reported or elicited during open-ended questioning, examination, or evaluation of a subject. (In order to prevent reporting bias, subjects should not be questioned regarding the specific occurrence of one or more AEs.)

